##### Augmented feedback

Provision of external augmented feedback has been shown to improve performance of motor skills, but can hinder learning if the individual becomes too dependent on it [56]. To decrease dependence and facilitate learning, the feedback should be 'faded', or gradually reduced, as training progresses [59]. In this study, faded augmented feedback will be provided to improve the speed of the grasping reactions. Subjects will be told their handrail-contact timing score after every trial during the first week, after every second trial during the second week, etc. Augmented feedback will not be required for the step training, as pilot testing has shown that subjects are typically well aware of the occurrence of multiple steps and foot collisions during training.

##### Instructions

Instructions should direct the learner's attention toward important aspects of the skill being learned. However, to promote optimal learning, complex skills should not be broken down into smaller sub-components, and instructions should refer instead to the 'whole response' [59]. Furthermore, instructions that provide the learner with an external focus promote learning better than instructions with an internal focus [60,61]. Therefore, in this study, subjects will be provided with generalised instructions regarding the task goals. Thus, for example, subjects will be given no specific instructions about weight shifting or control of the limb trajectory during stepping reactions, but will instead simply be told to take as few steps as possible or to avoid contacting the foam-rubber barriers. Where possible, subjects will be provided with an external focus, such as the handrail to be grasped or the foam blocks that they must avoid.

### Subject tolerance and acceptance

A pilot study was performed to evaluate the degree to which older adults with instability problems are willing and able to tolerate the training procedures. As described in more detail elsewhere (Maki et al., paper in review), the study involved eight older adults who were referred to a clinical falls prevention program, due to problems with instability, falling and/or fear of falling. Subjects were assigned, at random, to either the perturbation-based program or a program that focussed on training of rapid volitional stepping and grasping movements. The pilot results support the feasibility and safety of the perturbation-based program, and provide no evidence that balance-impaired older adults would be less able or willing to tolerate this approach in comparison to training of volitional movement. Compliance was very similar in the two groups. Moreover, no subjects indicated that they felt unsafe during the training, and there were no injuries or other adverse outcomes in either training program.

## Methods – Part B

### Experimental protocol to assess the training program

A randomised controlled trial will be performed to assess the efficacy of the perturbation-based training program. Ethical approval for this study was obtained from the Research Ethics Board of Sunnybrook Health Sciences Centre.

#### Recruitment of subjects

Community-dwelling older adults, aged 64–80 years, will be recruited via advertisements in local newspapers and seniors' residences and by word of mouth. All subjects will be mobile (not dependent on mobility aids) and will be able to stand (≥ 1 minute) and walk (≥ 10 m) without any assistance. To simplify training and assessment, the study will be restricted to persons who are right upper- and lower- limb dominant (as defined by the preferred limb for writing and kicking). In order to target an 'at risk' population, volunteers who respond affirmatively to any of the following questions will be included in the study:

• Have you fallen in the past 5 years?

• Have you lost your balance or almost fallen in recent memory?

• Have you reduced your activities or changed your lifestyle because you were concerned that you might fall?

• Do you ever feel unsteady when: getting in or out of a chair, changing direction when you are standing or walking, reaching for something above your head, or walking and talking to someone at the same time?

• Has anyone, such as a friend or family member, expressed concern that you may have problems with your balance or are at risk of falling?

Additionally, volunteers who report a decline in their balance greater than a 'moderate amount' in recent years, or have low balance confidence (Activity-specific Balance Confidence score less than 85% [62]), will be included in the study.

To avoid potential confounding effects on balance and to ensure a relatively homogeneous cohort, the following exclusion criteria will be applied: 1) current diagnosis of neurological or sensory disorders, diabetes, depression or osteoporosis; 2) uncorrected vision problems that impair ability to read, watch television, or drive a car; 3) recurrent dizziness; 4) cognitive impairment (standardized Mini-Mental State Examination [63] score < 24); and 5) joint replacement or joint fusion. To ensure that the subjects are sufficiently fit and healthy to tolerate the training program without adverse effects, volunteers who answer 'yes' to any items on the Physical Activity Readiness Questionnaire [64] will be asked to obtain approval from their doctor prior to participating in the study. To prevent potential confounding effects of other exercise programs, volunteers who regularly (≥ once per week) participate in a supervised exercise program will be excluded. Subjects who are unable to provide written informed consent (e.g. due to poor English language comprehension) will also be excluded.

#### Cohort descriptors

A number of measures will be collected for purposes of characterising the cohort, in terms of sensory, musculoskeletal, neuromotor and cognitive function, balance and mobility, anthropometrics, psychometrics, health status and lifestyle. As indicated in Table 2, a subset of these measures will also be used to compute an overall falls-risk score (FallScreen^© ^[65]), based on a database compiled from numerous prospective falls-prediction studies [66-69].

**Table 2 T2:** Cohort descriptors

**General domain**	**Specific domain**	**Instrument**
Anthropometrics		Weight^†^, height, arm span, and waist and hip circumference

Sensation	Vision	High- and low-contrast visual acuity^§^
		Edge contrast sensitivity (Melbourne Edge Test)^§^
		Depth perception^§^
	Vibration sense	200 Hz vibration at the knee^§^
	Proprioception^†^	Joint position matching task, left and right knee angle^§^
	Touch sensitivity	Monofilament test at the plantar heel [83]
	Vestibular	Vertical X-Writing Test (proxy measure) [84]

Musculoskeletal	Isometric strength^†^	Ankle dorsiflexion^§^
		Knee extension ^§^
	Lower-limb power^†^	Repeated Step-Up (proxy measure) [79]
	Flexibility^†^	Sit-and-reach test [78]

Neuromotor	Coordination	Finger-to-nose touch test [85]
	Simple reaction time^†^	Finger press^§^
		Foot pedal^§^

Cognitive	Cognitive function	Standardized Mini-Mental State Examination (sMMSE) [63]
	Memory and recall	Supraspan forward digit recall with motor component [86]
	Visuospatial memory	Backward digit recall [87]

Balance & mobility	Static balance^†^	Spontaneous postural sway, measured at pelvis; four conditions: eyes open or closed, standing on firm surface or foam^§^
	Dynamic balance^†^	Coordinated stability^§ ^(volitional centre-of-mass movement around a designated course)
		Maximal balance range^§ ^(range of forward and backward lean)
	Mobility^†^	Timed Up and Go [77]

Health and lifestyle	General health	Medical Outcomes Study, Short form (MOS SF-36) [88]
	Falls history	Custom-designed questionnaire
	Exercise behaviour	Physical Activity Scale for the Elderly (PASE) [89]
	Activities of daily living	Instrumental Activities of Daily Living [90]

Psychometrics	Balance confidence^†^	Activity-specific Balance Confidence questionnaire (ABC) [62]
	Trait anxiety	Endler Multi-dimensional Anxiety Scale – Trait (EMAS-T) [91]
	State anxiety^†‡^	Endler Multi-dimensional Anxiety Scale – State (EMAS-S) [91]
	Depression	Centre for Epidemiologic Studies Depression Scale (CES-D) [92]
	Personality	Neuroticism Extraversion Openness Five Factor Inventory (NEO-FFI^TM^) [93]
	Fear of falling and activity restriction	Survey of Activities and Fear of Falling in the Elderly (SAFFE) [94]

^†^These tests will be completed pre- and post-intervention

^‡^This questionnaire is administered immediately following balance testing

^§^These tests are part of the FallScreen© assessment [65, 95]

#### Intervention

Each training program will last six weeks, with three 30-minute sessions per week. This duration and intensity is similar to that used in previous perturbation-based training studies [34,35,39]. All subjects will be asked to refrain from initiating any other new exercise programs, or otherwise consciously changing their activity levels, during their participation in the study. For the perturbation-based training program, each session will consist of 2–3 minutes of preparation and instruction, 10–12 minutes of step training, 3–5 minutes of rest, and 10–12 minutes of grasping training. We aim to complete at least 24 trials of stepping and 24 trials of grasping per session (three sets of eight trials for each).

The control subjects will undergo a flexibility and relaxation program, and will receive the same degree of interaction with experimenters as those in the perturbation-training group. The first session of each week will involve 30 minutes of passive muscular relaxation exercises [70]. The second and third sessions will focus on lower- and upper-body flexibility exercises, respectively. In the flexibility sessions, a ten-minute warm-up (heart rate kept below 60% of maximum) will precede 15 minutes of stretching exercises, (two sets of 7–9 stretches for each muscle group, with each stretch held for 15 seconds). The control program is designed to involve a limited intensity of physical activity, so as to avoid bringing about any significant physiological changes. A similar, but more intense, flexibility and relaxation program failed to reduce falling [9], or brought about only moderate improvements in falls risk [71]. Subjects will be asked not to practice the relaxation or flexibility exercises outside of the scheduled sessions during the study.

#### Testing of compensatory stepping and grasping reactions

Two balance-laboratory assessments will be performed to evaluate the effects of the training on compensatory stepping and grasping. The first session will occur not more than one week before the start of training and the second no more than one week after the end of training. Two different types of balance perturbation will be used: waist-pulls and support-surface translations. Because support-surface translations are also used during the perturbation-based training, testing with surface translations will allow us to identify whether the targeted aspects of the change-in-support reactions were improved by the training. The waist pulls involve perturbation of the centre of mass (rather than the base of support), elicit different patterns of body motion and sensory drive, and evoke stepping and grasping reactions that differ in some key respects in comparison to reactions evoked by platform perturbation [72,73]; hence, the waist-pull tests will allow us to begin to examine whether any of the benefits of the training are generalisable to other balance-loss situations.

All laboratory tests will be performed with the subject standing at the centre of a large (2 × 2 m) computer-controlled motor-driven motion platform [17,74]. The waist-pull system is mounted on the motion platform, thereby allowing the type of perturbation to be varied unpredictably during testing (Figure 4). Waist-pull perturbations will be applied by dropping a weight (20% of body weight), attached to a belt worn around the pelvis via a custom-built cable and pulley system. Four cables are attached to the belt to allow perturbations to be delivered unpredictably forward, backward, left or right. The weight is dropped 40 cm for stepping trials and 30 cm for grasping trials. For the support-surface translations, we will use a displacement, velocity and acceleration of 0.18 m, 0.6 m/s and 2.0 m/s^2^, respectively, for forward translations (which evoke backward falling motion), and 0.27 m, 1.0 m/s and 3.0 m/s^2 ^for the other translation directions (backward, left, right). We know, from pilot tests and previous studies [22-24], that the selected waist-pull and surface-translation parameters are tolerated by older adults and will consistently evoke stepping or grasping reactions.

**Figure 4 F4:**
[figure not shown]
**Experimental set-up for testing of stepping and grasping reactions**. Schematic drawing showing the experimental set-up for the balance testing (performed at baseline and after the six weeks of training). The platform is semi-enclosed, with walls to the front and sides of the subject; for illustration purposes, the left wall has been rendered semi-transparent. The motion platform is controlled by a motor (located underneath the surface) to move unpredictably in one of the four directions shown. The cable-pull system also delivers unpredictable perturbations in these four directions. Four cables are attached to the belt at the waist, and are routed via a system of pulleys to a weight-drop apparatus that is located behind the front wall of the platform (out of the view of the subject). Prior to each trial, the experimenter manually connects one of the four cables to the weight. An electromagnet is then used to initiate the weight drop. When the weight is dropped, the subject is pulled unpredictably in one of the four directions, depending on which cable is attached to the weight. Prior to perturbation onset, an equivalent amount of slack (~2–4 cm) in each cable is maintained via a locking mechanism; hence, subjects are free to sway to an equal extent in any direction and cannot detect which cable is attached to the weight. During the testing of grasping reactions, a handrail (not shown) is mounted to the right of the subject (25% of body height from midline; height  of rail = 55% of body height) and foam blocks (40cm high) are placed around  the feet to deter stepping (similar to Figure 2B).

Perturbation direction and type (i.e. waist pull or surface translation) will be varied in an unpredictable pseudo-random sequence so as to prevent subjects from pre-planning their response. An initial set of 12 familiarisation trials will be completed at the start of each laboratory session in order to dampen within-session habituation effects [47]. Following this, three blocks of perturbation trials will be completed: 1) compensatory stepping during stance, 2) compensatory stepping while walking in-place, and 3) compensatory grasping during stance. Table 3 details the task conditions and numbers of trials completed in each trial block.

**Table 3 T3:** Balance tests performed before and after training

**Task conditions**	**Response observed**	**Perturbations and numbers of trials**^†^
*Familiarisation*: Stance, unconstrained arm and foot motion (instructed to react naturally)	not applicable	4 medium translations^‡ ^(F,B,L,R) 4 large translations^‡ ^(F,B,L,R) 4 waist pulls (F,B,L,R) *Total *= *12 trials*

*Trial block #1:* Stance, arm motion restricted, instructed to react naturally but minimise number of steps	Compensatory stepping main focus: multiple-step responses (a-p perturbations)	5 backward translations 3 forward translations 2 lateral translations (L,R)^§^ 4 translations, 2^nd ^waveform (F,B,L,R)^#^ 5 forward waist pulls 3 backward waist pulls 2 lateral waist pulls (L,R)^§^ *Total *= *24 trials*

*Trial block #2:* Walking in-place, arm motion restricted, instructed to react naturally but minimise number of steps	Compensatory stepping main focus: foot collisions (lateral perturbations)	5 leftward translations 3 rightward translations 2 a-p translations (F,B)^§^ 4 translations, 2^nd ^waveform (F,B,L,R)^#^ 5 rightward waist pulls 3 leftward waist pulls 2 a-p waist pulls (F,B)^§^ *Total *= *24 trials*

*Trial block #3:* Stance, foot motion restricted, instructed to recover balance by grasping handrail (at right of subject)	Compensatory grasping main focus: speed of grasping (a-p perturbations)	5 forward translations 4 backward translations^§^ 4 forward waist pulls^§^ 5 backward waist pulls *Total *= *18 trials*

^†^During trial blocks #1–3, the listed platform-translation and waist-pull perturbations are delivered in an unpredictable randomised sequence, in the directions indicated (F = forward, B = backward, L = left, R = right; a-p = antero-posterior)

^‡ ^The familiarisation block includes initial medium-magnitude platform perturbations, followed by the same large-magnitude perturbations that are used in the main trial blocks. The platform acceleration of the large perturbations (2.0 m/s^2 ^forward, 3.0 m/s^2 ^other directions) is 50% greater than the medium perturbations (1.3 m/s^2 ^forward, 2.0 m/s^2 ^other directions).

^§ ^These tests are included primarily for the purpose of increasing the unpredictability of the perturbation direction and will not be part of the main analysis

^# ^The 2^nd ^waveform tests will not be part of the main analysis, but are included to deter subjects from learning to use the deceleration of the platform to aid in recovering balance [46]. The usual waveform comprises a 300 ms acceleration pulse followed immediately by a 300 ms deceleration pulse. The 2^nd ^waveform comprises a 200 ms acceleration pulse and a 400 ms constant-velocity interval, prior to a 200 ms deceleration pulse. The acceleration magnitude for this second waveform ranges from 1.35 m/s^2 ^to 2.25 m/s^2^.

During compensatory stepping tests, subjects will be asked to respond to the balance perturbations naturally, but to minimise the number of steps taken if they do step. To restrict arm movement, they will hold a lightweight rod behind their back [74]. To deter conscious efforts to pre-plan or modulate the reactions, subjects will be required to perform a concurrent distraction task (counting backward by 3's from a 3-digit number randomly assigned at the start of the trial) while waiting for the perturbation, during the stance trials (blocks 1 and 3). In the second block of trials, they will perform a walk-in-place task, (lifting the feet in time with a metronome, 100 beats per minute) to increase the probability that a foot collision will occur [22]. For compensatory grasping trials, a handrail will be mounted to the right of the subject. Subjects will be instructed to grab the rail with the right hand as quickly as possible to recover balance, in response to the perturbation. They will be told not to step, and foam blocks will be placed around their feet to further deter stepping. A safety harness will be worn throughout all of the testing.

#### Outcome measures

The four primary outcome measures correspond to the specific aspects of change-in-support reactions that were targeted in the perturbation-based training program: 1) average number of 'extra' steps taken to recover balance, 2) frequency of foot collisions when responding to lateral perturbations, 3) frequency of additional lateral steps when responding to antero-posterior perturbations, and 4) handrail-contact time for grasping reactions. Secondary outcome measures relating to other features of the balance reactions will also be analysed. For compensatory stepping, these include the frequency and magnitude of anticipatory postural adjustments (APA), foot-off time, foot-contact time, step length and frequency of arm reactions. For compensatory grasping, we will analyse onset timing and magnitude of arm-muscle activation (biceps, medial deltoid), arm trajectory, and frequency of grasping errors (e.g, undershoot, overshoot, collision of hand with rail). The early 'automatic postural response' (which occurs in both stepping and grasping trials) will be analysed using centre-of-pressure measures and the latency and magnitude of the initial ankle-muscle activation (tibialis anterior, medial gastrocnemius).

The kinematic measures (step length, arm trajectory) will be determined by using a six-camera infrared motion-analysis system to record displacement of reflective markers placed bilaterally on the feet and arms. The behavioural measures (foot collisions, additional steps) will be determined using a computer-based algorithm to process the foot-marker kinematics; results will be verified by manual inspection of these data and associated video recordings by a blinded investigator. In addition, effectiveness of the stepping and grasping reactions in preventing "falls" will be analysed by using a load cell to monitor the force applied to the safety harness. Step timing, APAs and centre-of-pressure will be characterized using three force plates built into the surface of the motion platform. Handrail-contact timing will be determined from force-sensing resistors mounted on the rail. Muscle activation will be recorded bilaterally using surface electromyography (EMG). All timing measures will be defined in relation to onset of platform motion (measured with accelerometers) or onset of weight-drop (measured with a load cell). See previous articles for more details about the measurement and analysis methods [74-76].

Other secondary outcome measures will be analysed to evaluate whether the training had any benefits extending beyond effects on balance reactions. We will explore indirectly the effect on overall falls risk using the FallScreen^© ^battery noted earlier. In addition, we will explore effects on: 1) balance confidence (Activity-specific Balance Confidence questionnaire [62]); 2) mobility ('Timed Up & Go' test [77]); 3) flexibility (modified 'sit and reach' test [78]); and 4) lower-limb power (using the repeated step-up test [79] as a proxy measure [80]).

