#### Statistical analysis

The effect of the two training interventions on the outcome measures will be determined using repeated-measures analysis of variance (ANOVA) with two factors: 1) group (perturbation-based training versus control group), and 2) session (pre- versus post-training). Any of the cohort descriptors (measured at baseline, as detailed earlier) that show significant inter-group differences in preliminary univariate analyses will be included as covariates in the main analysis. As noted earlier, the control training program was specifically designed not to improve balance control; therefore, changes in the control group (pre- versus post-training) are expected to represent typical learning effects resulting from repeated exposure to the balance-assessment procedure, as well as possible 'placebo' effects associated with the interventions. Analysis of the group-by-session interaction will therefore reveal any real benefits resulting from the perturbation-based training intervention.

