#### Sample size estimate

To date, five subjects have completed the perturbation-based training and five have completed the control intervention. Sample size calculations for repeated measures ANOVA [81] were performed using the variance from these initial ten subjects. Separate calculations were performed using two of the primary outcome measures, so as to determine the sample-size requirements based on stepping reactions (average number of 'extra' steps taken to recover balance) and grasping reactions (handrail-contact time). For both calculations, probability of Type I error was 0.05, and probability of a Type II error was 0.2.

A previous study of older adults showed that the average number of 'extra' steps taken to recover balance was 1.21 in 'fallers' and 0.825 in 'non-fallers' [25]. This suggests that a reduction equal to 0.5 steps, due to the perturbation-based training, will have functional significance. Using this value, in combination with the initial variance estimate (SD = 0.44 steps), it was determined that 15 subjects per group will be required. For grasping responses, the previous study [25] indicated that handrail-contact time was delayed by 50 ms, on average, in the 'fallers'. Detection of a training effect of this size, given the initial variance estimate (SD = 39 ms), requires a sample of only 12 subjects per group. Thus, to ensure sufficient statistical power for both stepping and grasping measures, it appears that 15 subjects per group will be required. However, sample-size requirements will be re-evaluated at two intermediate stages, i.e. after completing 10 and 15 subjects in each group. If any subjects are still enrolled in either training program when the new estimate for the required number of subjects is reached, these remaining subjects will complete the study and the tested sample will exceed the estimated requirement.

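### Four unranked primary outcomes with no success rule, sized at the full 0.05 on only two of them: if any one suffices, the chance of a false positive is about 13–19%

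*Protocol article*

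**What the plan says.** The Outcome measures section introduces the list with "The four primary outcome measures correspond to the specific aspects of change-in-support reactions that were targeted in the perturbation-based training program" and then numbers four measures: extra steps, foot collisions under lateral perturbation, additional lateral steps under antero-posterior perturbation, and handrail-contact time. None is placed above another.

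The Statistical analysis section applies a repeated-measures ANOVA with two factors, group and session, to the outcome measures. It concludes: "Analysis of the group-by-session interaction will therefore reveal any real benefits resulting from the perturbation-based training intervention". It gives no significance level and no rule for combining the four results.

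The Sample size estimate section says "Separate calculations were performed using two of the primary outcome measures", namely extra steps and handrail-contact time, and "For both calculations, probability of Type I error was 0.05, and probability of a Type II error was 0.2". It then presents 15 per group as enough for stepping and for grasping measures alike.

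The section on testing of reactions adds: "Two different types of balance perturbation will be used: waist-pulls and support-surface translations". It gives the two types different purposes. For translations, "testing with surface translations will allow us to identify whether the targeted aspects of the change-in-support reactions were improved by the training". For waist pulls, "the waist-pull tests will allow us to begin to examine whether any of the benefits of the training are generalisable to other balance-loss situations".

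**The concern.** With four unranked primary outcomes and a full 0.05 behind each calculation, the plan as printed offers four chances at a primary result. A reader of the final report could not tell whether one significant interaction out of four means that the training worked or is what chance would often produce.

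The power statement has a related weakness. Two of the three primary stepping measures, foot collisions and additional lateral steps, were not part of any calculation. A claim of adequate power for stepping measures in general therefore goes further than the calculations behind it.

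**Working it through.** **Inputs from the Sample size estimate section.** Extra steps: difference 0.5, SD 0.44, 15 per group. Handrail-contact time: difference 50 ms, SD 39 ms, 12 per group. Type I error 0.05, Type II error 0.2. The article does not say whether the tests are one- or two-sided, or whether the SD is that of the pre-post change.

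**Step 1: reproduce the stated sizes.** With two groups and two sessions, the interaction test is a two-sample comparison of change scores, so n per group = 2(z₁₋α/₂ + z₁₋β)²(SD/Δ)².
- Extra steps: 2 × (1.960 + 0.842)² × (0.44/0.5)² = 15.70 × 0.7744 = 12.2, so 13 (14 with the t distribution). Stated: 15.
- Handrail-contact time: 15.70 × (39/50)² = 15.70 × 0.6084 = 9.6, so 10 (11 with t). Stated: 12.

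Both are within two of the stated figures. A one-sided 0.05 gives 10 and 8, which does not match. I therefore read the plan as two-sided 0.05 per outcome, with the SDs as SDs of change. If they were single-session SDs, the required n for extra steps would depend on the pre-post correlation: 19 at 0.3, 14 at 0.5 and 9 at 0.7.

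**Step 2: error rate if any one of four suffices.** For independent tests it is 1 − 0.95⁴ = 18.5%. Counting only results in favour of training, it is 1 − 0.975⁴ = 9.6%. For correlated outcomes I simulated four two-sample t-tests with 15 per group (60,000 runs per setting). The article gives no correlations, so these are assumptions.

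| Correlation | At least one false positive, two-sided | In favour of training |
|---|---|---|
| 0 | 18.5% | 9.6% |
| 0.3 | 17.4% | 8.7% |
| 0.5 | 15.8% | 7.9% |
| 0.7 | 13.0% | 6.4% |

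The nominal values are 5% and 2.5%.

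**Step 3: power at 15 per group after adjustment (noncentral t).**

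| Two-sided alpha | 0.5 steps | 50 ms |
|---|---|---|
| 0.05 | 85% | 92% |
| 0.025 | 77% | 87% |
| 0.0125 | 67% | 79% |

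The strictest Holm step for four outcomes is 0.05/4 = 0.0125. These last figures are floors: an outcome tested after others have been rejected faces 0.05/3, 0.025 or 0.05.

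**Step 4: the opposite rule.** If all four had to succeed, error would not be inflated, but power would be the problem. For the two sized outcomes alone, joint power under independence is 0.852 × 0.923 = 0.79, before adding two outcomes with no power basis.

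**The case against.** The article is a condensed protocol. Its 0.05 is an input to the sample size, not a stated level for the final tests, and an unseen analysis plan may contain an adjustment. No any-one-wins rule is printed. The sentence on the interaction mainly explains why change in the control group is subtracted, and the hypothesis speaks of stepping and grasping together. This stands to the extent that the inflation is conditional on how success is read, and silence on adjustment is not in itself the fault. What remains is what the article does fix: four equal primaries and a sample size built on an unshared 0.05. A later adjustment would lower the published power, as step 3 shows.

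A reader might also infer eight primary tests, four outcomes under two perturbation types, and a false efficacy rate as high as 1 − 0.95⁸ = 34%. The documents do not support that. Perturbation type is not a factor in the ANOVA, and waist pulls are given a separate, exploratory-sounding role. Independence is implausible because the same subjects supply every measure and an additional lateral step is itself an extra step. The 34% also counts errors against training, which are not efficacy claims. It is true that Table 3 excludes only some of the waist-pull trials from the main analysis, so their status needs a sentence, but that does not make them primary.

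Nor can a reader conclude that collisions are underpowered by any particular amount. The article gives no collision rate, so any such figure would rest on invented inputs.

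**Conclusion.** The point holds in a limited form. The four primaries are unranked, no success rule or multiplicity control is given, and the trial is sized at the full 0.05 on two of them. If one significant interaction is enough, the chance of at least one false positive is about 13–19% two-sided, or about 6–10% in favour of training, for assumed common correlations from 0.7 to 0. If every outcome must succeed, the error rate is not inflated but the power statement no longer applies. Under either reading that statement covers extra steps and handrail-contact time only. The power figures assume two-sided tests and that the stated SDs are SDs of change.

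**What to change.** 1. Apply Holm across the four primary outcomes at an overall two-sided 0.05. If the sponsor prefers, test them in a fixed order starting with extra steps and handrail-contact time, with the order set without reference to group results.
2. State that surface translations carry the primary test and that waist pulls are a secondary analysis of generalisability. This follows the roles that the article already gives them.
3. Limit the power statement to extra steps and handrail-contact time, and say that foot collisions and additional lateral steps have no power basis.
4. Restate power at alpha 0.0125: about 67% for 0.5 steps and 79% for 50 ms at 15 per group, beside 85% and 92% at 0.05. Say which SD was used.

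The cost is a change of wording and a less favourable power figure, below the 80% target at the strictest step. No new data or subjects are needed. Should the sponsor wish to restore 80% at that step, the t-based sizes are 19 per group for extra steps and 16 for handrail-contact time. The re-evaluations already planned after 10 and 15 subjects per group are a natural place to use the adjusted alpha.
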